##### Social support in coping with the disease

The Berlin Social Support Scales (BSSS) [68] differ from other questionnaire methods for social support by their multidimensional approach, that is, by their cognitive and behavioural aspects. AYA are asked whom they relate their answers to. The original questionnaire consists of six scales (Perceived, Received and Achieved Support, Need and Search for Support, Protective Buffering). In this study the subscale “Actually Received Support, Recipient” is used. The subscale includes 11 items plus a general score, and the four-step answer format ranges from “strongly disagree” to “strongly agree”. The subscale together with the general score shows an internal consistency of α = .83 [68].

##### Intervention satisfaction

Participants’ satisfaction with the Internet-based intervention will be assessed with the Client Satisfaction Questionnaire adapted to Internet-based interventions (CSQ-I) [69]. The self-report questionnaire consists of eight items that are rated on a 5-point Likert scale from 1 = “does not apply to me” to 4 = “does totally apply to me”. The scale shows a very good reliability, indicated by McDonald ω values of .93 to .95. The CSQ-I will be used during the intervention (t1 and t2), only for participants receiving youthCOACH_CD_.

##### Therapeutic alliance

In the present study, therapeutic alliance between client and e-Coach/the Internet-based intervention will be assessed with an adapted version of the Working Alliance Inventory-Short Revised (WAI-SR) questionnaire [70]. The 12-item self-report questionnaire is rated on a 5-point Likert scale (1 = “rarely” to 5 = “all the time”). For the German version, internal consistencies between α = .81 and α = .91 were reported for the three subscales (Agreement on Tasks, Agreement on Goals, and Development of an Affective Bond) and an internal consistency between α = .90 and α = .93 for the total score [71]. The WAI-SR will be completed by the intervention group only.

##### Behavioural activation

The Behavioral Activation for Depression Scale (BADS) [72] examines the role of controlling aversive stimuli and avoidance behaviour in depression. As such, it observes changes in activation within treatment. The BADS consists of 25 questions, each rated on a 7-point scale ranging from 0 = “not at all” to 6 = “completely”. The total score demonstrated acceptable internal consistency (α = .79) [73].

##### Automatic thoughts

The Automatic Thoughts Questionnaire-Revised (ATQ-R) [74] records the influence of the intervention on automatic thoughts. The German version of the questionnaire consists of 21 items and can be rated on a 5-point scale between “not at all” and “all the time” [75]. The internal consistencies of the scales of the German version are between α = .75 and α = .89. All scales showed significant correlations with depressiveness and differentiated between adolescents aged between 11 and 16 years with higher and lower depressive symptom severity [75].

##### Quality of life

The generic EuroQol Five-Dimensional Questionnaire (EQ-5D), measuring quality of life, is a short instrument that provides information on health states as a basis for the estimation of quality-adjusted life years (QALYs) [76]. A version for respondents aged 8 to 18 years is the EQ-5D-Youth version (EQ-5D-Y) [77, 78], developed based on the standard EQ-5D [79]. The available utility value sets for adults have been found to be not applicable to children and adolescents [80]. In the absence of a utility value set for children and adolescents in Germany [77], the health states will be valued by means of the visual analogue scale (VAS) of the EQ-5D-Y. The EQ-5D-Y consists of five items and can be evaluated by a 3-point scale (“no problems”, “some problems”, “a lot of problems”). The EQ-5D-Y dimensions were found to be reliable on test-retest (in 69.8–93.8% of Italian youths and in 86.2–99.7% of Spanish respondents) [79]. The EQ-5D-Y not only serves as a secondary outcome, but is also used for economic evaluation.

#### Caregiver reports

##### Depressive and anxiety symptom severity

In order to be able to record the severity of depression and anxiety symptoms not only in self-judgment but also in caregiver reports, a caregiver/adult reference person of the participant is asked to rate the Screen for Child Anxiety Related Emotional Disorders (SCARED) [81] questionnaire and the Mood and Feelings Questionnaire (MFQ) [82].

The SCARED, which examines the third-party rating of anxiety symptoms of the last 3 months, consists of five items and is scored on a 3-point scale from “not true or rare” to “accurate or frequent”. The scale has an acceptable to good internal consistency (α = .74 to α = .93) [83, 84].

The MFQ parent report of depressive symptoms is useful both for preliminary screening and to monitor change in symptomatology [82]. The MFQ short version consists of 13 items, which are rated by a reference person on a 3-point scale from “not true” to “true”. The internal consistency of the original scale is good, with α = .91 to α = .96 [85, 86].

##### Social support

The BSSS [68] will be answered by AYA participants (more information can be found in the section “Secondary outcomes”) and caregivers. The BSSS caregiver report is used to identify how the caregivers assess their own social support for the adolescent. Internal consistency for the 11-item scale “Actually Received Support” is good, with α = .75 [68].

##### Traumatic experiences

Whether the treatment has an influence on the effects of traumatic experiences due to the chronic somatic condition is explored by the stress symptom list of the Child and Adolescent Trauma Screen-Caregiver (CATS-C-D) for AYA aged 7–17 years, from the point of view of the caregivers. The questions about trauma-specific symptoms are introduced by the request that the caregivers refer to the currently most stressful event for the respective AYA with regard to their chronic somatic condition and describe it briefly. The severity of the symptom scale can be rated from 0 = “never” to 3 = “almost always”. The 20-item symptom score of the observer report has proven good reliability with α = .87. Limitations of the functional level in different areas of life are also assessed [64].

#### Adverse events

##### Subjective side effects

Possible unwanted/negative effects of the intervention (t2, t3, and t4, only for participants receiving youthCOACH_CD_) are assessed by the 23 item Inventory for Recording Negative Effects of Online Interventions (INEP-On). This is an adapted version of the Inventory for recording negative effects of psychotherapy that is specifically adjusted for online interventions [87]. Eleven items are rated on a 7-point bipolar scale (− 3 = “better; is totally true” to + 3 = “worse; is totally true”) and 12 items on a 4-point Likert scale (0 = “no agreement at all” to 3 = “total agreement”). The original scale shows a high internal consistency of α = .85 [87].

##### Symptom deterioration

The PHQ-ADS [50] is not only used as a primary or secondary outcome, depending on the assessment time point, but also to determine depression and anxiety symptom deterioration.

##### Internet usage behaviour

In order to explore the change in Internet usage due to treatment, the questionnaire Internet-Use Expectancies Scale (IUES) [88] is used. The IUES consists of eight items with a two-factor structure, that is positive and avoidance expectancies. The items can each be rated on a 6-point Likert scale. Both factors have good reliability (“positive expectancies”, Cronbach’s α = .83 and “avoidance expectancies”, Cronbach’s α = .76) [88]. In addition to the questionnaire, open questions are asked about the duration of use for the Internet and the smartphone, either privately or educationally/professionally.

##### Suicidal ideations

Notwithstanding that suicidality is defined as an exclusion criterion, suicidal ideation might occur during the course of the study and will therefore be monitored closely by means of the PHQ-9 Item 9 at all assessment points (t0–t4). A score ≥ 1 on the suicidality item of PHQ-9 (“Thoughts that you would be better off dead or of hurting yourself in some way?”) leads to the Beck Depression Inventory-Revised (BDI-II) [54] suicidality item (Item 9; BDI-II item = 0: “I’m not thinking of harming myself.”, BDI-II item = 1: “I have thoughts of killing myself, but I would not carry them out”, BDI-II item = 2: “I would like to kill myself”, BDI-II item = 3: “I would kill myself if I had the chance”) [89]. A score ≥ 1 on the BDI-II suicidality item results in a standardized suicide prevention protocol.

Participants screening positive (BDI-II Item 9 ≥ 1) receive an online information letter with detailed information on available and appropriate health services with the advice to use professional help. Participants are informed that youthCOACH_CD_ is not optimized for suicidal ideation management.

In the case of BDI-II Item 9 ≥ 2, participants automatically receive, in addition to the information letter with detailed information on available and appropriate health services, an individual safety plan to fill out (numbers of personal contacts, counselling, medical on-call and emergency numbers), and the project team will follow a detailed, stepped suicide prevention protocol. These participants will be contacted by one of three licensed (child and adolescent) psychotherapists via telephone and interviewed in regard to suicidality. In case of acute suicidality, participants are directed to appropriate on-site mental health care services, when they are compliant. In case of acute suicidality and perceived non-compliance, contact details of participants will be immediately transferred to emergency services in order to secure the safety of participants and initiate appropriate crises intervention; non-compliant participants will be subsequently excluded from the trial. Participants who do not indicate acute suicidal ideations and express compliance will proceed with the study routine.

In order to counteract unexpected side effects or to be able to react when they occur, it is possible for the study participants to contact the study team during working hours by telephone or e-mail. Participants are referred to a nationwide and 24/7 emergency doctor’s telephone hotline and receive detailed information about treatment options. If participants indicate suicidality, the above-mentioned prevention protocol takes effect.

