### Outcome measurements

#### Primary outcome: depressive and anxiety symptom severity

The primary outcome is the combined depressive and anxiety symptom severity at t2, assessed with the PHQ-ADS [50]. Depression and anxiety symptoms at all other assessments will be considered as secondary outcomes. PHQ-ADS is the combined sum score of the questionnaires GAD-7 and PHQ-9 as a composite measure of depression and anxiety, with good internal consistency (α = .88 to .92) [50].

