### Statistical analyses

All statistical analyses are processed by a biostatistician who is blinded with regard to group assignment. Patterns of missing data will be examined. Multiple imputation with predictive mean matching will be performed to account for missing data. All analyses will be conducted on a two-sided level of significance (α = .05). Participant characteristics will be described descriptively. Rates of patient-reported adverse events will be compared.

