### Effectiveness analysis

There will be no interim evaluation of the primary outcome. All statistical analyses will be performed based on the intention-to-treat (ITT) principle. Additional per protocol analyses will be conducted in order to examine the effects of youthCOACH_CD_ in case of patients adhering to the intervention protocol. Participants who completed at least 80% of the intervention are defined as intervention completers (= per protocol).

The primary outcome will be analysed using a hierarchical linear model to account for clustering with the PHQ-ADS score at t2 as dependent variable and the baseline value as covariate, adjusting for sex, age, and chronic somatic condition. Standardized mean differences and 95% CIs will be calculated to measure the between-group effect size at post-treatment (t2) and follow-up (t3, t4). Secondary outcomes will be analysed accordingly.

Exploratory mediation and moderator analyses involving the primary and secondary outcomes as well as demographic data will be conducted. Moderator and subgroup analyses will be attempted in case of a sufficiently large sample size.

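### The suicide-prevention rule takes some randomised participants out of the trial, not only out of treatment, and so ends their follow-up for an outcome-related reason (minor)

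*Protocol article*

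**What the plan says.** The Suicidal ideations section sets out a stepped procedure. PHQ-9 Item 9 is checked at t0 to t4. A score of 1 or more leads to the BDI-II suicidality item, and a BDI-II score of 2 or more leads to a telephone interview by a licensed psychotherapist. The outcome of that interview decides what follows:

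- Acutely suicidal and compliant: the participant is directed to on-site care. The article does not state the participant's further study status.
- Acutely suicidal and perceived as non-compliant: contact details go to emergency services, and "non-compliant participants will be subsequently excluded from the trial".
- Neither: "Participants who do not indicate acute suicidal ideations and express compliance will proceed with the study routine".

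The procedure can also start between assessments, when a participant contacts the study team: "If participants indicate suicidality, the above-mentioned prevention protocol takes effect".

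On analysis, the article states "All statistical analyses will be performed based on the intention-to-treat (ITT) principle" and "Multiple imputation with predictive mean matching will be performed to account for missing data". On safety, it states "Rates of patient-reported adverse events will be compared". The PHQ-ADS is the primary outcome at t2, a secondary outcome at the other assessments, and the measure of symptom deterioration.

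**The concern.** The wording merges two decisions that should be kept apart: stopping the study treatment and stopping observation. A clinician may have good reason to stop the online programme in a crisis. It does not follow that outcome collection should stop, and in the TAU+ arm there is no study programme to stop.

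The rule is also informative about outcome. It selects on extreme severity of a symptom that the PHQ-ADS contains, and on refusal of help. The refusal concerns crisis care. It is neither a refusal of questionnaires nor a withdrawal of consent, so the missing follow-up is created by the plan and is at least partly avoidable. Values lost this way may well not be missing at random.

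What is at stake is mainly objective 5 (safety compared with TAU+) and objective 4 (cost-effectiveness over 12 months). The negative-effects inventory (INEP-On) is given to the intervention arm only, so the comparison between arms leans on the repeated PHQ-ADS and suicidality measures, which are the ones that stop. An admission that follows the emergency referral would fall in the period no longer observed.

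**Working it through.** No figure stated in the article depends on this rule, so there is none to reproduce. The planned 212 participants (106 per arm) are the same with or without it. The check is a reading of the text, followed by a count of the follow-up lost per case.

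**Does the rule act after randomisation, and in both arms?** The Discussion says that randomised participants are those who finish the baseline assessment. A case found at t0 would therefore normally come before randomisation, and excluding it is harmless. From t1 onwards the rule acts on randomised participants. Nothing limits it to the iCBT arm.

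**Is the trigger linked to the outcome?** Yes: "PHQ-ADS is the combined sum score of the questionnaires GAD-7 and PHQ-9", and Item 9 is one of the nine PHQ-9 items. For the same reason the PHQ-ADS at the triggering assessment is normally already recorded. If the trigger is a contact between assessments, the last recorded score is the one from the previous assessment.

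**Does any other text keep these participants in follow-up?** None that is shown. The only group expressly said to continue is the one without acute ideation that expresses compliance.

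**Follow-up lost per case.** Inputs: assessments at 6 weeks (t1), 12 weeks (t2), 6 months (t3) and 12 months (t4), from Objectives and Study design, with 6 and 12 months taken as 26 and 52 weeks. Weeks lost = 52 − week of trigger.

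| Trigger at | Weeks lost | Share of 52 weeks | Later assessments lost (of 4 after randomisation) |
|---|---|---|---|
| t1 | 52 − 6 = 46 | 88% | 3 |
| t2 | 52 − 12 = 40 | 77% | 2 |
| t3 | 52 − 26 = 26 | 50% | 1 |
| t4 | 0 | 0% | 0 |

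**Effect on a deterioration rate.** One later event that goes unseen changes an arm's rate by 1/106 = 0.94 percentage points. This applies only to a participant not already counted as deteriorated at the triggering assessment.

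**Effect on the primary outcome.** A trigger at t2 or later leaves the t2 score in place. Only exclusion before t2 can remove it, and that value is then imputed. The documents give neither the number of such cases nor how far an imputed score would miss the true one, so no bias figure can be derived.

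**The case against.** The strongest case against is that this is a rare event, already handled. To be excluded, a participant who passed screening (Item 9 no higher than 1) must later score on Item 9, reach 2 on the BDI-II item, be judged acutely suicidal by telephone, and also be seen as non-compliant. The serious event is itself detected before exclusion. Analyses are intention-to-treat with imputation. The article is condensed and points to a detailed suicide prevention protocol that is not shown, which may say how data are handled afterwards. Whether to go on contacting such a participant is a clinical decision, in a trial with ethics approval and an independent monitoring board.

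Most of this stands, and it limits the point to a minor one. It does not remove it. The article states the exclusion as a rule, so this is not a detail left for another document. Imputation keeps these participants in the analysis set but cannot show what happened to them after the crisis.

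Three stronger readings are tempting, and the documents do not support them:

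- A reader might infer that the rule breaks intention-to-treat. The article does not say that excluded participants leave the analysis set, and its analysis statements imply that they stay in with imputed values.
- A reader might infer a bias in the primary result. Its size and even its sign are unknown: a high score at t1 can inform the imputation, and crisis care may improve the later score. If cases balance between arms, the shifts would tend to cancel.
- A reader might infer that caregiver reports are lost needlessly because they do not depend on the participant. The article gives only their purpose ("In order to be able to record the severity of depression and anxiety symptoms not only in self-judgment but also in caregiver reports"). The caregiver schedule is in a table that is not shown, and participants from age 16 consent for themselves, so caregiver data on an excluded participant may need that person's agreement.

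**Conclusion.** The point holds as a minor one. As written, the plan ends follow-up of randomised participants in either arm for an outcome-related reason that is neither withdrawal of consent nor refusal of assessments. The loss per case is 46, 40 or 26 of 52 weeks for a trigger at t1, t2 or t3. It falls on later deterioration and suicidality data, t3 and t4 outcomes, and service use after the crisis. The effect on the primary outcome is expected to be negligible.

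This rests on taking the exclusion literally, as the end of scheduled assessments, and on few cases occurring. The documents give no rate. The emergency referral is appropriate and is not in question.

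**What to change.** Replace the exclusion from the trial with wording such as: *the study intervention is stopped where clinically indicated (iCBT arm); in both arms, data already collected are kept and the remaining scheduled assessments are offered unless consent is withdrawn or contact is judged clinically inappropriate; each such event is reported by randomised arm.* Caregiver assessments should continue only where consent covers them.

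The cost is one or two sentences. No new instrument is needed, and neither the emergency procedure nor the sample size changes. The downside is some further contact with a vulnerable subgroup, possibly for little extra data. Reporting the events by arm serves the safety objective even if few later assessments are obtained.

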#### Economic evaluation: use and costs of medical and psychosocial services

The Child and Adolescent Mental Health Services Receipt Inventory (CAMHSRI-DE) will be applied to collect information on the clients’ use of health and social services. The extent of service usage is determined on the basis of frequency and duration for eight service categories (inpatient medical services, outpatient medical services, social services—inpatient and outpatient, other inpatient services, school-based services, school types, and medication intake) [90]. The frequency and duration for each health care service will be interpolated for a reference period of 6 months. The CAMHSRI-DE is based on the Client Sociodemographic and Service Receipt Inventory (CSSRI) [91, 92], adjusted for children and adolescents with mental health problems in the German health care system [90]. Costs of service use will be estimated on the basis of unit cost information [93].

### Statistical analyses

All statistical analyses are processed by a biostatistician who is blinded with regard to group assignment. Patterns of missing data will be examined. Multiple imputation with predictive mean matching will be performed to account for missing data. All analyses will be conducted on a two-sided level of significance (α = .05). Participant characteristics will be described descriptively. Rates of patient-reported adverse events will be compared.

### Effectiveness analysis

There will be no interim evaluation of the primary outcome. All statistical analyses will be performed based on the intention-to-treat (ITT) principle. Additional per protocol analyses will be conducted in order to examine the effects of youthCOACH_CD_ in case of patients adhering to the intervention protocol. Participants who completed at least 80% of the intervention are defined as intervention completers (= per protocol).

The primary outcome will be analysed using a hierarchical linear model to account for clustering with the PHQ-ADS score at t2 as dependent variable and the baseline value as covariate, adjusting for sex, age, and chronic somatic condition. Standardized mean differences and 95% CIs will be calculated to measure the between-group effect size at post-treatment (t2) and follow-up (t3, t4). Secondary outcomes will be analysed accordingly.

Exploratory mediation and moderator analyses involving the primary and secondary outcomes as well as demographic data will be conducted. Moderator and subgroup analyses will be attempted in case of a sufficiently large sample size.

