### Study interventions

#### Intervention condition

The intervention group receives the iCBT plus treatment as usual (TAU) and is compared to a control group, which receives TAU+. youthCOACH_CD_, developed by the Department of Clinical Psychology and Psychotherapy (FL, AG, MD, HB) consists of an introductory session with information about the online-based intervention and seven modules of approximately 50 to 70 min processing time each. Modules can be repeated as often as desired. The modules cover the topics motivation and resources, behavioural activation, understanding and coping with anxiety and depression, emotion regulation, communication, and social support as well as relapse prevention. The intervention is presented via information texts, videos, audio recordings, photos, metaphors, and therapeutic homework. The content of the intervention is based on CBT principles for depression and anxiety, including elements of psychoeducation, individual resources of the AYA, active coping (problem solving), restructuring of stressful disease-related thoughts, communication training, relaxation, and behaviour activation to model adaptive coping strategies.

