#### Guidance

The intervention is therapist-guided by e-Coaches, who report semi-standardized feedback after each completed module on the intervention platform to the participant using an e-Coach manual. The e-Coach manual is standardized to guarantee protocol adherence by the e-Coaches. e-Coaches are graduates of a Master’s Degree in Psychology or Pedagogy, who are enrolled in a training program in CBT with children and adolescents, closely supervised by licensed psychotherapists. The feedback content matches the participants’ tasks and is aimed to support adherence to treatment. The feedback also includes positive reinforcement to motivate participants to continue the intervention. For further questions, participants and e-Coaches can communicate via the intervention platform. e-Coaches will also send reminders to participants who do not complete intervention modules at the scheduled time via e-mail and telephone. The weekly schedule for processing a module is set by the participants themselves at the end of the previous module. In order to promote commitment, the intervention is blocked for the participant after three reminders without the participant reacting. For participants who indicate that they wish to continue, youthCOACH_CD_ will be reactivated. Table 2 shows the intervention structure and implementation.

**Table 2 Tab2:** Intervention structure, technical implementations, and support

Intervention structure	
• Seven weekly modules (50-70 min.)	
Implemented elements	
• Guidance by trained and supervised e-Coaches (graduates of a Master’s Degree, who are enrolled in a training program in CBT with children and adolescents)	
• One feedback message per module by e-Coaches	
• Reminders by the e-Coach if the modules are not processed at a date set in advance by the participant to promote adherence	
• Deactivation and reactivation when modules are not processed and three unsuccessful reminders	
• Answers to additional questions from e-Coaches and the study team	
• Tight security procedure for suicidal clues	
• Weekly challenges/ homework	
• Diaries via a mobile app with daily reminders	
• Information given by text and videos	
• Audio guided exercises	
• Patient examples written and presented as audio recordings	
• Metaphors, quizzes and conditional content	
• Modules can be repeated as often as desired	

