#### TAU+

TAU+ includes all routine care services for somatic and mental health problems. TAU+ can vary depending on the clinic, location, care options, and barriers of care as well as the specific needs of AYA. TAU is supplemented (enhanced, +) by screening for symptoms of anxiety and depression and by information letters on evidence-based mental health care options.

TAU+ is not defined a priori, but is recorded alongside the health economic evaluation and can thus be described post hoc descriptively.

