### Sample size/power calculation

A clinically significant effect of at least *d* = .50 for the mean difference between the groups is assumed, which refers to the severity of the primary outcome, i.e. a PHQ-ADS sum score [50] at 12 weeks post-randomization (t2). The assumption for the clinically significant effect is based on a meta-analysis by Ebert and colleagues, who reported a moderate to high effect size of *g* = .72 (95% confidence interval [CI] .55–.90) for Internet and computer-based CBT in the reduction of depressive and anxiety symptoms in youth [39], based on trials comparing Internet- and computer-based CBT to non-active control conditions (waitlist; placebo). However, given that TAU usually results in higher effect sizes compared to waitlist control groups, we regard a lower than *g* = .72 effect size as clinically relevant. The sample size calculation was carried out by an external statistician from the Department of Psychological Research Methods at Ulm University (MM) based on a power of .90 and α < .05 (two tailed) considering the cluster structure (intra-class correlation [ICC] = .02) of the different prevalence numbers of these chronic somatic conditions, resulting in 166 participants equally randomized to both conditions (2 × *n* = 83). According to a meta-analysis, studies evaluating the efficacy and effectiveness of computer-based psychological treatments for depression with therapeutic support reported a drop-out rate of approximately 28% [51]. For this reason, the sample is increased by 28%, resulting in a total of *N* = 212 participants (2 × *n* = 106).

Various measures will be taken to minimize study drop-outs. Participants receive €10 as an expense allowance at all psychometric assessment points. After successful completion of all assessments, participants can also take part in a prize draw. Moreover, in order to avoid drop-outs in the intervention group, youthCOACH_CD_ was designed to persuade the target group of AYA using e.g. multimedia features such as videos and audios as well as prompts and reminders [52].

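### The additional per-protocol analysis selects on completion in the iCBT arm only, so it is not a randomised comparison and does not isolate the effect in adherent patients

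*Protocol article*

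**What the plan says.** The section Effectiveness analysis makes intention to treat the basis: "All statistical analyses will be performed based on the intention-to-treat (ITT) principle". It then adds a second analysis and gives its purpose: "Additional per protocol analyses will be conducted in order to examine the effects of youthCOACH_CD_ in case of patients adhering to the intervention protocol". The set is fixed by one rule: "Participants who completed at least 80% of the intervention are defined as intervention completers (= per protocol".

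The only model described is a hierarchical linear model "with the PHQ-ADS score at t2 as dependent variable and the baseline value as covariate, adjusting for sex, age, and chronic somatic condition". No separate model, weighting or instrument is described for the per-protocol analysis, and no criterion for control participants.

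The programme "consists of an introductory session with information about the online-based intervention and seven modules of approximately 50 to 70 min processing time each". Under Guidance, pacing is left to the participant: "The weekly schedule for processing a module is set by the participants themselves at the end of the previous module". Access is blocked after three unanswered reminders and can be reactivated on request. The primary outcome is measured at t2, 12 weeks after randomisation. No date is given by which the 80% must be reached.

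The comparator has no module content and no adherence standard: "TAU+ is not defined a priori, but is recorded alongside the health economic evaluation".

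**The concern.** The rule uses behaviour after randomisation and can remove people from one arm only. Applied literally to both arms it would leave no controls at all. The comparison that remains sets iCBT participants who kept going against everyone in TAU+, including those who would have stopped had they been offered the programme. The contrast that matches the stated purpose is completers against the controls who would have completed, and the planned analysis does not form that group.

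Keeping going with seven modules plausibly depends on motivation and on how mood develops in the first weeks. Baseline score, sex, age and condition capture these only in part. What they leave unexplained appears in the per-protocol estimate as if it were a treatment effect. At stake is the one planned estimate that claims to describe adherent patients, a figure that readers of a digital-intervention trial are likely to pick up.

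**Working it through.** **The plan's own figures.** The article gives no figure for the per-protocol analysis. The arm size used below comes from its sample size section, which reproduces. For d = .50, power .90 and two-sided α = .05, n per arm = 2 × ((1.960 + 1.282)/0.50)² = 84.06. Multiplying by (1 − ICC) = 0.98 gives 82.4, rounded up to 83, so 166 in total. Then 166 × 1.28 = 212.5, taken as 212, or 106 per arm. The factor (1 − ICC) is a reconstruction; the article does not state its formula.

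**Inputs that the documents do not give (assumptions).**
- c, the share of the iCBT arm reaching 80%: 0.5, range 0.4 to 0.7.
- g, the gap in untreated outcome between completers and non-completers, in residual SD after the model's covariates, positive when completers do better: 0.3, range 0.2 to 0.5, with 0 and negative values considered separately.

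**Bias under no effect.** Let completers have mean prognosis μC and non-completers μN, with g = μC − μN. By randomisation the control mean is c·μC + (1 − c)·μN. Completers minus all controls is therefore μC − [c·μC + (1 − c)·μN] = (1 − c)·g.

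**Rejection rate under no effect.** SE = √(1/(106c) + 1/106), shift = (1 − c)·g/SE, rejection = P(Z > 1.96 − shift) + P(Z < −1.96 − shift).

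| c | g | Bias (SD) | SE | Shift | Rejection |
|---|---|---|---|---|---|
| 0.5 | 0.3 | 0.15 | 0.168 | 0.89 | 14.5% |
| 0.7 | 0.2 | 0.06 | 0.151 | 0.40 | 7% |
| 0.4 | 0.5 | 0.30 | 0.182 | 1.65 | 38% |
| any | 0 | 0 | – | 0 | 5% |
| 0.5 | −0.3 | −0.15 | 0.168 | −0.89 | 14.5%, against iCBT |

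The second and third rows are the ends of the range. With g = 0.1 the rejection rate is only 5.5% to 6.3% for c between 0.4 and 0.7.

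**With the plan's 28% loss.** 106 × 0.72 ≈ 76 per arm. For c = 0.5 and g = 0.3, SE = √(1/38 + 1/76) = 0.199, shift = 0.15/0.199 = 0.755, and rejection is about 12%. The upper end of the range falls from 38% to about 29%. This uses observed cases only. The article plans multiple imputation, so the figure could lie between the two.

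**A second model.** Completion was linked to the covariate-adjusted outcome through a latent normal variable with correlation ρ and completer share p. The bias is then ρ·φ(z)/p with z = z(1 − p). For p = 0.60 to 0.72 and ρ = 0.1 to 0.4 it is 0.05 to 0.26 SD. Simulation with 106 per arm and 20,000 runs per setting gives rejection of about 6% to 38%, and about 5% at ρ = 0.

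**Meaning of 80%.** 0.8 × 7 = 5.6, so 6 of 7 modules. If the introductory session counts, 0.8 × 8 = 6.4, so 7 of 8 units. The rule does not say which.

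**The case against.** Several points on the other side have force.

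- **The analysis is additional.** No listed objective asks for an effect in adherers, and the sample size does not rest on one. This stands. A reader might infer that the trial's main result is biased; the documents do not support that, because the primary analysis is by intention to treat.
- **The handling of controls is not written down.** This stands as far as it goes: that all controls are kept is inferred. But the article does state the rule and equates it with per protocol, and no reading of that rule selects comparable controls. The problem lies in what is stated, not in detail left to an unseen analysis plan.
- **The direction is assumed.** This also stands. A reader might infer that the analysis must favour the intervention. It does so only if completers have the better residual prognosis. Participants who improve early and stop would reverse the sign.
- **The model adjusts for baseline score.** Only the unexplained part of the gap counts, which is why g is defined above as a residual gap. A crude gap put into the same formula would overstate the bias.
- **Completion after t2.** A reader might infer that late completion distorts the set. Self-set pacing and reactivation make it possible, but seven weekly modules before a 12-week assessment leave about five weeks of slack, and nothing shows that it matters in practice. It justifies a cut-off date, no more.
- **A complier-average effect has its own bias.** With an 80% cut-off it assumes no effect below the cut-off. If non-completers gain δ, the estimate exceeds the effect in completers by (1 − c)·δ/c, which equals δ when c = 0.5. This stands and limits how the remedy may be presented.

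**Conclusion.** The point holds for the additional analysis only. As written, the per-protocol set depends on post-randomisation behaviour that only one arm can show. The comparison is therefore not protected by randomisation and does not estimate what its stated purpose asks for. This conclusion needs no assumption about direction.

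The size does rest on assumptions, since the documents give neither a completion share nor a prognosis gap. With 50% completing and a residual gap of 0.3 SD, the spurious effect is 0.15 SD and the two-sided rejection rate under no effect about 14% (about 12% with 28% loss). Set against the planning value ("A clinically significant effect of at least *d* = .50 for the mean difference between the groups is assumed"), that is 0.15/0.50 = 30%, taking the residual SD as equal to the outcome SD. Over 40% to 70% completing and gaps of 0.2 to 0.5 SD the range is 0.06 to 0.30 SD and 7% to 38%. With no residual gap there is no bias. A bias in favour of iCBT is the likelier direction, but it is not established.

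The change should be made, but it is not critical, because the intention-to-treat conclusion does not depend on this analysis.

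**What to change.** - Estimate the effect in adherers as a complier-average causal effect on all randomised participants, with allocation as instrument and the primary model's covariates. TAU+ does not include the programme, so one-sided non-compliance is a reasonable basis for the monotonicity assumption. If the intervention does nothing, the intention-to-treat difference is zero in expectation and so is its numerator; one-armed selection does not enter.
- Define receipt as at least 80% of the intervention completed by t2, and say whether that means 6 of 7 modules or 7 of 8 units.
- State the exclusion restriction (no effect below the threshold), say that benefit from partial use would inflate the estimate, and repeat the analysis with a lower threshold.
- Keep the comparison of completers with controls only as a supportive description, labelled as non-randomised.

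The cost is a small amount of analysis work on data that are collected anyway. The confidence interval widens: the standard error is roughly that of the intention-to-treat difference divided by c, so about double at c = 0.5. The exclusion restriction cannot be tested, so the result should not be presented as free of assumptions. Weighting for completion is a possible alternative, but it relies on having measured what drives completion.
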